The secondary outcomes were: (1) neck pain VAS score during neck movement, assessed 1 week after US-FHR; (2) pain VAS score at rest, assessed 15 min and 1 week after the procedure; (3) blood flow volume at the FHR-treated site, measured by ultrasound immediately and 1 week after US-FHR; (4) ADL, assessed using the PDI-5-J before and 1 week after US-FHR; and (5) Surface temperature, measured by thermographic camera before, immediately after, and one week after US-FHR. All secondary outcomes were compared with baseline values. Pain VAS scores were determined by measuring the distance (mm) from the “no pain” anchor and the patient’s mark on a 100-mm line, providing a score range of 0–100. Pain at rest and during movement were scored separately. Blood flow in the transverse cervical or dorsal scapular artery was evaluated immediately before and 2 min after US-FHR during the first and second visits. Arterial blood flow at the planned US-FHR site was measured as follows. First, an image of the vessel along its long axis was obtained, and the maximum diameter was recorded. After confirming arterial blood flow using the Superb Microvascular Imaging (SMI) mode, measurements were performed in Pulsed Wave mode. To ensure reliability, the sampling gate was set to two-thirds of the vessel diameter, and the angle correction was maintained below 60°. The blood flow waveform was observed, and the start and end points of one cardiac cycle were visually determined to trace a single heartbeat. Vessel diameters at the measurement site were recorded. To accurately capture the vessel lumen, the SMI flow display was removed, and the image was magnified to enhance clarity. The vessel diameter was measured as the distance between the inner walls of the lumen, and the cross-sectional area was calculated assuming a circular shape. The ultrasound system software then automatically calculated and displayed the corresponding blood flow volumes, which were recorded. At the second visit, blood flow was measured at the same site as during the first visit by reproducing identical imaging conditions. To ensure consistency, images from the previous measurement were printed, and confirmation was made that the trapezius and supraspinatus muscles, and either the transverse cervical or dorsal scapular artery, were visualized in the same manner before proceeding with the measurement. The PDI-5-J, assessed from the first visit (surveyed before US-FHR) to the second visit, was also included as a secondary outcome measure. The PDI-5-J (five-item Japanese version of the Pain Disability Index) is a self-report questionnaire designed to evaluate the degree to which pain interferes with five domains of daily activities: Family/Home Responsibilities, Recreation, Social Activity, Occupation, and Self-Care. Respondents rate their level of disability in each domain on an 11-point scale ranging from 0 (no disability) to 10 (total disability). The total score ranges 0–50, with higher scores indicating a greater degree of pain-related disability. The PDI-5-J was developed by omitting the items on sexual behavior and life-support activities from the original seven-item PDI, reflecting cultural considerations and respondent comfort in Japan. The PDI-5-J has demonstrated good reliability and validity for evaluating pain-related interference with daily activities among Japanese individuals with chronic pain. The painful site was identified, and its surface temperature was measured using a thermographic camera (FLIR C5™, FLIR® Systems, Inc.) before, immediately after, and one week after US-FHR. The use of analgesics was permitted during the study period; however, FHR, trigger point injections using local anesthetics or steroids, and acupuncture therapy were not allowed during the time between the first and second visits.

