**Data management and statistical analysis**

Sample size calculation

The sample size was calculated using a one-sample t-test to determine whether the mean change in VAS score from baseline differed from zero. Based on a previous study (Fujita N, et al., J Clin Anesth. 2016;31:149–153), the expected mean change in VAS score was set at 20 mm with a standard deviation of 35 mm, yielding a standardized effect size of 0.57. The significance level (alpha) was set at 0.05 (two-tailed), and the target statistical power was 0.8. The calculated sample size was 28 participants. Assuming an approximate 20% dropout rate, the required number of participants was set at 35.

If the actual number of enrolled participants is lower than anticipated, the sample size will be recalculated and may be modified accordingly.

Statistical analysis

Categorical and continuous variables is summarized as numbers (percentages) or medians (IQR), as appropriate. Pain VAS scores, blood flow volumes and surface temperature measures immediately and 1 week after US-FHR were compared with baseline values using the Wilcoxon signed-rank test. P-values were adjusted for multiple comparisons using the Bonferroni correction. Differences in PDI-5-J scores between baseline and the second visit were also assessed using the Wilcoxon signed-rank test. For all analyses, a P-value < 0.05 was considered statistically significant. All analyses were performed using GraphPad Prism (version 10.6.1, GraphPad Software, Boston, MA, USA).

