**Quality assurance**

Data analysis

CRFs will be prepared for data analysis. The entries and any corrections on the CRFs will be completed by the investigators. The investigators will complete the CRFs for each participant promptly after each observation and examination. The original CRFs will be stored at [name] Pain Clinic. Any corrections will be made by striking through the original entry with a single line and recording the reason for the correction, the date and time of the correction, and the identity of the person making the correction in the margin. Data analysis will be performed by an investigator who is responsible for data collection but is not involved in performing the fascia hydrorelease procedures.

Discontinuation criteria

The study intervention for an individual participant will be discontinued if any of the following occur during the study period:

1)The participant ceases to attend study visits during the study period.

2)The participant or their legally authorized representative requests withdrawal from the study (withdrawal of consent).

3)It is found that the participant does not meet the inclusion criteria or meets any exclusion criterion.

4)The study as a whole is terminated for any reason.

In addition, the principal investigator or sub-investigators may discontinue the study intervention for a participant at their discretion if any of the following occur:

5) An adverse event occurs that makes continuation of the study difficult or inappropriate.

6) Worsening of complications related to comorbid conditions is observed, making continuation of the study difficult.

7) The participant is judged not to be compliant with the instructions of the treating physician.

8) Any other reason for which the principal investigator or sub-investigators judge that continuation of the study is not feasible.

If none of the events 1)–8) occur and the participant completes the entire study period including the follow-up assessments, participation in the study will be considered complete.

Obligations to report to the ethics committee

The following events will be reported to the ethics committee:

(i) Any amendments to the study protocol.

(ii) Premature termination or completion of the study.

(iii) Any change in the principal investigator.

Study-related documents and data

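### Blood flow volume, a secondary outcome, is read live by hand at time points evident to the reader, and the plan describes no masking; reading stored images in coded random order would be a cheap improvement

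*Protocol*

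**What the plan says.** Blood flow volume at the treated site is the third of five secondary outcomes (Protocol, Study goals and objectives; Methodology, outcome measurements). It is read before the injection, 2 min after it in the same session, and at the one-week visit.

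The Methodology fixes several steps: the sampling gate relative to vessel diameter, an upper limit on the correction angle, magnification, and inner-wall diameter. It leaves others to the person at the machine. For the waveform, "the start and end points of one cardiac cycle were visually determined to trace a single heartbeat". The diameter is placed by hand, the area is then taken as a circle, and the angle may lie anywhere under 60°. Only after these choices does automation begin: "The ultrasound system software then automatically calculated and displayed the corresponding blood flow volumes, which were recorded".

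At the second visit, "images from the previous measurement were printed, and confirmation was made that the trapezius and supraspinatus muscles" and the target artery looked the same as before, and only then was the measurement made.

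On roles, Quality assurance says: "Data analysis will be performed by an investigator who is responsible for data collection but is not involved in performing the fascia hydrorelease procedures". The document does not say who takes the flow readings. It describes no reading with the time point hidden, no offline reading and no reliability check.

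**The concern.** Flow is the outcome that most directly tests the proposed mechanism, and the Project summary presents the haemodynamic measurements as objective. Yet each value rests on choices made by eye by someone who will normally know whether the injection has been given. The Rationale reports that the investigators have already seen arterial flow improve after the procedure, so the expected direction is known in advance.

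The study is single-arm, and flow is tested as a change from baseline. No comparison group shares the same reading habits, so a consistent lean cannot be told apart from a treatment effect. Averaging more beats would reduce noise but would not remove a lean in one direction.

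**Working it through.** **1. The plan's own figure.** The only sample size is for the pain VAS, where "the expected mean change in VAS score was set at 20 mm with a standard deviation of 35 mm". With two-sided alpha 0.05 and a power target of 0.80, the plan arrives at 28 evaluable patients and enrols 35 to allow for 20% dropout. The effect size is 20/35 = 0.571. A one-sample t-test (noncentral t) needs n = 27 (power 0.815), and n = 28 gives power 0.830. Inflation for dropout is 28/0.8 = 35. The figures are reproduced to within one patient. The document gives no SD, measurement error or sample size for flow, so 28 and 35 serve below only as the number of patients.

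**2. Is the time point evident to the reader?** The document does not say so, but it follows from the procedure. The baseline and 2-min readings fall on either side of the injection in one session. At the second visit the reader has a print from the earlier measurement. The role separation in Quality assurance keeps the injector out of the analysis, but the analyst also collects data. That is not masking.

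**3. Diameter.** Flow = mean velocity × π × diameter² / 4, so with velocity unchanged the false change is (1 + e)² − 1 for a proportional diameter lean e.

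| Lean e | Calculation | False change in flow | Lean on an assumed 2 mm vessel |
|---|---|---|---|
| 3% | 1.03² = 1.061 | +6.1% | 0.06 mm |
| 5% | 1.05² = 1.1025 | +10.3% | 0.10 mm |
| 10% | 1.10² = 1.21 | +21% | 0.20 mm |

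The leans and the 2 mm vessel are assumptions; the document gives neither.

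**4. Angle.** Corrected velocity is proportional to 1/cos(angle), so setting the angle too high by δ multiplies flow by cos θ / cos(θ + δ). At a true 55°, an excess of 2° gives +5.3% and 3° gives +8.2%. At 45°, an excess of 5° gives +10.0%. All these settings respect the 60° limit.

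**5. Would a lean reach significance?** That depends on the lean relative to the SD of the change in flow, which is not given. The table shows the probability of a significant result when there is no true change. A t-test stands in for the planned signed-rank test. Bonferroni is taken over two time points (0.025), which is an assumption because the plan does not state the number of comparisons.

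| Lean / SD of change | n = 35, 0.05 | n = 35, 0.025 | n = 28, 0.05 | n = 28, 0.025 |
|---|---|---|---|---|
| 0.1 | 0.09 | 0.05 | 0.08 | 0.04 |
| 0.2 | 0.21 | 0.14 | 0.18 | 0.11 |
| 0.3 | 0.41 | 0.30 | 0.33 | 0.23 |
| 0.5 | 0.82 | 0.73 | 0.72 | 0.61 |

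A 10% flow lean is 10/20 = 0.5 SD if the SD of change is 20%, but only 10/50 = 0.2 SD if it is 50%. The answer therefore runs from unlikely to likely across plausible inputs.

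**The case against.** The strongest reply is that nothing here is misstated. The protocol standardises gate, angle limit, magnification, inner-wall placement and view, the software does the arithmetic, and flow is one secondary outcome in an open single-arm study. This stands as a limit on how serious the point is. It does not supply masking. Nor can a later analysis plan, because the way values are read is a matter of conduct.

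A reader might infer that the week-1 prints themselves push the readings towards an increase. The text does not support this. The prints are described only as a check on view, which reduces error from measuring at a different place, and the document does not say that they show calipers or values. Even if they did, anchoring on a baseline image would pull towards no change, and the text does not say which image was printed. The prints also have no bearing on the 2-min reading.

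Two practical objections stand in part. Injected saline around the artery may be visible at 2 min and reveal the time point. And the non-injecting investigator is responsible for data collection, so may have acquired the images and may recognise them.

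**Conclusion.** The point holds as a cheap improvement to a secondary outcome. Flow readings depend on hand-set diameter, heartbeat limits and angle, are made with the time point evident, and have no masking and no control arm to absorb a systematic lean. A diameter lean of 3% to 10% would by itself produce about 6% to 21% more flow. This rests on the circular-area formula in the protocol and on assumed leans.

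Three stronger readings are not supported:
- that such a lean exists, since the document gives nothing from which to estimate one;
- that it would tend to be significant, since the SD of change is not given and the probabilities above run from 0.04 to 0.82;
- that flow is the only instrument-based evidence, since surface temperature by thermographic camera is also a secondary outcome.

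The primary outcome, movement pain marked by the patient on the VAS, is not affected.

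**What to change.** 1. Keep the week-1 prints for positioning, but print the anatomical view without calipers, diameter, trace or flow value.
2. Take the analysed diameter and heartbeat trace from stored images, cropped to the lumen where possible, coded and in random order, with patient, date and time point hidden. The reader should be an existing investigator who does not inject and, where possible, did not acquire those images. Keep the live values as a secondary record.
3. Report two remaining limits: masking may be incomplete at 2 min if saline is visible, and the angle set live stays unmasked.

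The cost is a few sentences in the Methodology and some offline reading. With one image set at each of three time points, that is 3 × 35 = 105 sets. No staff or patient procedures are added.

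The fix assumes that suitable measurement images were stored. The protocol mentions prints and procedure videos, which may not be enough, and much of the Methodology is in the past tense, so readings may already have been taken. If suitable images do not exist, state that flow was read unmasked and do not present it as objective evidence without that qualification.

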**Safety considerations**

Adverse events are defined as any undesirable occurrences, including side effects. Potential adverse events associated with US-FHR include bleeding, hematoma, and infection at the treatment site. In the event of an adverse event, appropriate management will be initiated promptly. For bleeding or hematoma, compression hemostasis will be performed, followed by careful observation for any additional bleeding. The treated area will be examined at the one-week follow-up visit to assess for residual bleeding. At the same visit, the US-FHR site will also be inspected for signs of infection, such as erythema, warmth, or swelling, and further examination or treatment will be provided if necessary. The presence or absence of adverse events will be recorded in the Case Report Form (CRF).

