**Follow-up**

The treated area will be observed for approximately 20 minutes after the US-FHR procedure to confirm that there are no changes in the overall condition, including the absence of any adverse events. At the follow-up visit one week after US-FHR, the treated area will again be examined for signs of infection such as redness, warmth, or swelling, and additional treatment or examination will be provided if necessary.

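### Adverse events that arise and resolve between the 20-minute observation and the 1-week visit, or are not local, are not actively sought and may be under-counted

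*Protocol*

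**What the plan says.** Protocol, Safety considerations, gives a broad definition: "Adverse events are defined as any undesirable occurrences, including side effects". It then names the expected events: "Potential adverse events associated with US-FHR include bleeding, hematoma, and infection at the treatment site".

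Two active detection steps are described.

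- **After the injection** (Follow-up): "The treated area will be observed for approximately 20 minutes after the US-FHR procedure". The same sentence extends this check to the patient's general state and to any adverse event.
- **At 1 week** (Safety considerations): "The treated area will be examined at the one-week follow-up visit to assess for residual bleeding", and "the US-FHR site will also be inspected for signs of infection, such as erythema, warmth, or swelling". The Follow-up section repeats the infection part only: "the treated area will again be examined for signs of infection such as redness, warmth, or swelling".

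The recording rule is general: "The presence or absence of adverse events will be recorded in the Case Report Form (CRF"). It is not restricted to findings visible at a visit. The protocol describes no question about the interval, no diary, no telephone contact and no instruction to report symptoms.

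**The concern.** The definition covers anything undesirable that happens to the patient after the injection. The described search covers the first 20 minutes or so and then the state of the skin and tissue at one place a week later. A bruise that appears that evening and fades by day 5, a two-day flare of pain, or a general symptom at home fits the definition but leaves nothing for the 1-week examination to find.

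Any error from this gap runs towards fewer events. The Project summary says the study aims to clarify whether the procedure can serve as a safe option. There is no comparison group under the same detection method, so under-detection would not cancel out. An analysis plan cannot repair this later, because events nobody asked about are not in the data.

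**Working it through.** **Step 1. Set definition, search and record side by side.**

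| Element | Scope in time | Scope in kind |
|---|---|---|
| Definition (Safety considerations) | no limit | any undesirable occurrence |
| Early observation (Follow-up) | about 20 minutes | treated area, overall condition, any adverse event |
| 1-week examination (Safety considerations, Follow-up) | what is present at that visit | treated area: remaining bleeding, signs of infection |
| CRF item (Safety considerations) | no limit stated | any adverse event |

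The first and last rows are broad. The two search rows leave out an event that starts after the observation and ends before the visit, and after the first 20 minutes they leave out anything not local. For these events the CRF depends on the patient volunteering them or an investigator choosing to ask.

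**Step 2. Check whether other steps fill the gap.** Methodology schedules pain scores at 15 minutes and 1 week, with none in between. Quality assurance has the CRF completed promptly after each observation and examination, which adds no inquiry about the interval. Prompt management (Safety considerations) and discontinuation for an adverse event (Quality assurance) apply once an event is known. They do not say how it becomes known.

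**Step 3. Size.** The protocol gives no adverse event rate, so there is no safety figure to reproduce. The only input taken from it is the planned enrolment, which reproduces: 28 / (1 − 0.20) = 35. The rest is an illustration on assumed values.

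- p = true proportion of patients with an event arising after the 20-minute observation (assumed).
- f = share of those events that resolve before 1 week and go unrecorded (assumed).
- Recorded rate q = p(1 − f).
- Chance of recording no such event in 35 patients = (1 − q)^35.

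| p | f | q | chance of none recorded |
|---|---|---|---|
| 10% | 0 | 10% | 2.5% |
| 10% | 25% | 7.5% | 6.5% |
| 10% | 50% | 5% | 16.6% |
| 10% | 75% | 2.5% | 41.2% |
| 5% | 0 | 5% | 16.6% |
| 5% | 25% | 3.75% | 26.2% |
| 5% | 50% | 2.5% | 41.2% |
| 5% | 75% | 1.25% | 64.4% |

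Example: p = 10%, f = 50% gives q = 0.10 × 0.50 = 0.05 and 0.95^35 = 0.166.

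The same relation affects how a clean result reads. With 0 of 35 recorded, the exact two-sided 95% upper limit for the *recorded* rate is 1 − 0.025^(1/35) = 10.0%. If half of the events went unrecorded, the matching limit for *occurrence* is 10.0% / (1 − 0.50) = 20%. With f = 0 there is no bias.

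**The case against.** The strongest reply has five parts.

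1. **The CRF item is unrestricted.** A reader might infer that an event counts only if it is still visible at 1 week, so that a resolved bruise would be entered as absent. The text does not say this. A site that knows of a resolved event must record it. This stands, and it is why the point is about eliciting events and not about which events qualify.
2. **The check for remaining bleeding follows directly on the management of a bleed.** It reads most naturally as follow-up of a known bleed, not as a rule for deciding whether an event occurred. This also stands, so that step should be left as it is. On that reading, however, a late bleed in a patient who was clear at 20 minutes is not explicitly sought at 1 week.
3. **The argument is partly from silence.** The CRF and consent forms are not shown and could contain a question or an instruction to report. The 1-week visit is also a natural moment to mention a problem. This is fair, and it limits the claim to what the protocol describes. The protocol does fix what is to be examined at that visit, and questioning is not part of it.
4. **No adverse event rate is a primary or secondary outcome, and no analysis of one is specified.** This stands. The efficacy conclusions are untouched. What is at stake is the safety statement announced in the Project summary.
5. **The magnitude is assumed.** This stands. It is also tempting to set 20 minutes against the 10,080 minutes in a week and call coverage 0.2%. That compares clock time. It is not a detection probability, because events in the interval can still be reported at the visit.

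**Conclusion.** The point holds in a limited form. The protocol defines adverse events broadly but describes an active search of only two kinds: about 20 minutes of observation, and an examination of the treated area at 1 week. Events that arise and resolve in between, or are not local, may go unrecorded, and any such error lowers the count.

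The documents do not support the stronger statements that such events *are* missed or that a reported rate *is* biased downward. The share of resolved events that would be volunteered is unknown, and if it is all of them there is no loss. The tabulated figures rest on assumed values of p and f and on 35 patients with follow-up, and they show scale only.

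This is a data-collection weakness worth correcting because the remedy is cheap. It does not threaten the primary analysis.

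**What to change.** In Safety considerations and Follow-up, keep the site examination and the existing bleeding follow-up, and add a standard step at the 1-week visit:

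- an open question to every participant about anything undesirable since the injection;
- then specific prompts on bleeding or bruising, signs of infection, and increased pain;
- onset and resolution dates for each event on the CRF.

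State that adverse events are reported as cumulative occurrence from injection to the 1-week visit, including resolved events, and give the number of participants questioned.

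It is not clear whether data collection is still open: Study design describes patients presenting up to 28 February 2025 in the past tense, while Duration of the project has recruitment completed by 31 March 2026. If collection is complete without such questioning, describe the safety result as findings at 20 minutes and at 1 week plus spontaneously reported events, and do not call it cumulative incidence.

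Cost: a wording change, added CRF fields and a few minutes at a visit that already takes place. The drawbacks are reliance on 7-day recall and a possibly less favourable event count. No treatment step changes.
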